## Abstract

**Background:**

Mental health disorders (MHDs) remain a leading cause of the global burden of diseases. Early identification of neurobiological mechanisms mediating a risk for MHDs is key to reducing a lifetime burden. Recent findings emphasize the locus coeruleus-norepinephrine (LC-NE) system as a neuromodulator of arousal translating acute stress responses into neuronal excitability. We propose that individual differences in LC-NE functioning can explain a differential susceptibility to psychological adversity, which mediates the development of transdiagnostic psychopathology in early childhood.

**Objective:**

The primary objective of LOCUS-MENTAL is to assess LC-NE functioning in preschoolers as a predictor of later psychopathology. This will be applied to generate an objective tool of individual early risk prediction, supporting targeted prevention of MHD.

**Methods:**

LOCUS-MENTAL includes 4 work packages. The centerpiece is an accelerated longitudinal study, in which a cohort of 300 preschool-aged children (aged 4‐6 years) will be recruited and followed up across 3 assessment waves, each one year apart. This will characterize developmental trajectories from 4 to 8 years of age. The primary outcome is the prediction of transdiagnostic psychopathology by pupillometry-derived LC-NE functioning. Transdiagnostic psychopathology is assessed by the Child Behavior Checklist (CBCL), while LC-NE functioning is assessed with pupillometry that includes core metrics of baseline pupil size (BPS) and stimulus-evoked pupillary response (SEPR). Cross-lagged panel models will be applied to the longitudinal data for quantifying causal effects between LC-NE functioning, childhood adversity, and psychopathology. Normative modeling and classification approaches will estimate an individual risk prediction based on pupillometric metrics of LC-NE functioning. The pupillometric battery has 4 passive auditory and visual paradigms. This battery will be validated with a multitrait-multimethod design that combines pupillometry with neurophysiological measures in electroencephalography, behavioral and cognitive measures, and neurocognitive paradigms. The study was approved by the Ethics Committee of the Faculty of Medicine at Goethe University Hospital (2024‐2160). Written informed consent will be obtained from caregivers and verbal assent by the children.

**Results:**

The study was funded in September 2024. Participant enrollment for the validation phase commenced in August 2025. As of February 2026, 82 participants were assessed, with a target of reaching 90 by the end of February 2026. Statistical analysis of the validation phase is planned for March 2026, with results aimed for publication in a peer-reviewed journal by the end of 2026. The longitudinal study is scheduled to start in April 2026 with completion in March 2029.

**Conclusions:**

The LOCUS-MENTAL study will establish whether LC-NE functioning provides a validated biomarker for detecting early psychopathology. The associated pupillometry provides a feasible and scalable test for identifying high-risk developmental trajectories in preschool children, which can be translated to clinical practice. The resulting risk assessment tool could facilitate a shift toward objective screening for mental health risks that enables targeted prevention with evidence-based treatment before diagnosis onset. This could prevent sequential comorbidity and reduce the lifetime burden of MHDs.

## Introduction

### Background

Mental health disorders (MHDs) describe enduring altered cognition, emotion, and behavior and remain a leading cause of the global burden of diseases. Recently, the locus coeruleus norepinephrine system (LC-NE) has been established as a modulator of sensory processing that translates acute stress responses into neuronal excitability. We propose this LC-NE functioning to explain a differential susceptibility to psychosocial adversity that underlies dispositional risks for MHD (Figure 1). LOCUS-MENTAL will put this to the test. We will assess LC-NE functioning in preschoolers as a predictor of later psychopathology. We will use pupillometry as a feasible neuroimaging technique to quantify LC-NE functioning in preschool children. LOCUS-MENTAL ultimately aims to generate an objective tool of individual risk prediction that informs a targeted prevention of lifetime MHD.

**Figure 1. F1:**
[figure not shown]
Theoretical model of LOCUS-MENTAL. Locus coeruleus-norepinephrine (LC-NE) functioning as a neurobiological mechanism in a developmental model of dispositional risks and stress, in which LC-NE functioning predicts psychopathology. LC-NE: locus coeruleus-norepinephrine.

LOCUS-MENTAL uses a transdiagnostic, dimensional, and developmental approach to investigate LC-NE functioning as a predictor of MHD. Variations of LC-NE functioning have been associated with phenotypes of psychopathology [1-3]. Our work validated pupillometry as a feasible method to assess LC-NE functioning, which will now be scaled to the application in an outpatient clinic for early detection in the general population [4,5]. Preschool children will be assessed in an accelerated longitudinal study to reveal prospective effects of LC-NE functioning on psychopathology in the school age. These key concepts are discussed below.

### Advancing Mental Disorders to a Transdiagnostic, Developmental Psychopathology

Comorbidity describes the co-occurrence of more than one diagnosis of MHD. Comorbidity is common, associated with more impairment and worse lifetime outcomes [6]. We lack the evidence to effectively treat MHD comorbidity at the time of this writing [7]. This may originate from conceiving MHD as independent diagnoses in clinical classification systems, which emphasized a focus on isolated diagnoses. In contrast, transdiagnostic psychopathology uses MHD comorbidity patterns to derive overarching factors. A bi-factor model with 3 factors showed the best fit in children [8]. An internalizing factor describes problems within individuals (depression and anxiety), whereas an externalizing factor describes problems between individuals (conduct problems and attention deficit hyperactivity disorder). Positive correlations between internalizing and externalizing established a superordinate p-factor that describes a liability for MHD. These 3 factors are continuous dimensions, in which manifestations below clinical thresholds are of prognostic relevance [9]. This transdiagnostic and dimensional perspective is expected to expose etiological mechanisms across MHD [10].

Comorbidity of MHD may further represent an endpoint where a secondary diagnosis arises because of a preceding primary diagnosis. This sequential comorbidity emphasizes a developmental perspective on MHD [11]. Most adults presenting comorbidity received an initial diagnosis in childhood, and half of all initial diagnoses occur before adolescence [6]. The preschool age may provide a sensible phase to identify mechanisms that influence developmental trajectories of lifetime psychopathology [12]. In addition, preschoolers differ in their risk for psychopathology even for shared psychosocial adversity [13]. This has been attributed to a differential susceptibility that explains an interaction of dispositional risks and stress [14]. We aim to identify a neurobiological mechanism of differential susceptibility [15] that mediates the impact of stress and contributes to the development of psychopathology.

### LC-NE in the Translation of Sensory Input to Neurophysiological Excitability

The LC-NE system is a neuromodulatory network orchestrating the brain’s response to sensory stimuli [16]. The LC-NE comprises the bilateral pontine locus coeruleus (LC) and its projections, which is the primary source of cerebral norepinephrine. Neuroimaging has suggested a bidirectional connectivity of the LC with the anterior cingulate cortex (ACC), thalamus, cerebellum, and the temporoparietal junction [17]. Compared to the substantia nigra, another neuromodulatory nucleus, the LC has shown increased connectivity to the visual, parietal, and motor cortices and the cerebellum [18]. This suggests a relative focus of the LC in earlier stages of sensory processing that perpetuates cognition and behavior.

The Adaptive Gain Theory (AGT) describes LC-NE functioning in cognition and behavior as a performance optimizer with 2 interchanging modes [19]. An exploration mode describes LC-NE tonic activity with a variable low frequency (1‐5 Hz) that corresponds to arousal levels [20]. In contrast, an exploitation mode describes LC-NE phasic activity with transient frequency and amplitude bursts that enhance the sensory processing of task-relevant stimuli [21]. At the system level, LC-NE activity reflects alerting attention [22]. At the neuron level, this has been elaborated to a mechanism of sensory selectivity. LC-NE tonic and phasic activity release norepinephrine which causes an autoinhibition of spontaneous neuronal activity and an excitation of input-driven activity [23]. This specific mechanism of neuronal gain modulation emphasizes a sensory processing of salience [24]. In the glutamate-emphasizes-noradrenergic-effects model [25], a salience is neurochemically indicated by a release of glutamate and can be independent of top-down control [24]. Under relative arousal, LC-NE activity initiates a positive feedback loop of glutamate and norepinephrine interactions that leads to excitatory hot spots of functional activity and biases large-scale networks [26] toward sensory processing of salient stimuli [27]. It has been observed that, in mice, a moderate stimulation of LC-NE activity enhanced thalamic feature selectivity, increased information transmission, and led to improved perceptual performance [28]. LC-NE functioning has been established as a key modulator of arousal and sensory processing with subsequent effects on perception and behavior [16,29].

### Pupillometry Reliably Measures LC-NE Functioning in Clinical Settings

LC-NE activity causes a dilation of the eye’s pupil. This pathway is indirect, as the LC-NE inhibits the Edinger-Westphal nucleus that typically emphasizes pupil constriction [30]. Pupil dilation has historically been used as an indicator of arousal and cognitive load [31]. Recently, pupil dilation has been differentiated into a baseline pupil size (BPS) and a stimulus-evoked pupillary response (SEPR), which index changes in LC-NE tonic and phasic activity, respectively [32]. These indices are assessed by pupillometry in video-based eye tracking. A study of combined functional magnetic resonance imaging and pupillometry showed a correlation of the LC’s signal with pupil dilation during the resting state (BPS) and with pupil dilation to oddball stimuli (SEPR) [33]. In a nonhuman primate model, an LC-NE stimulation predicted pupil dilation after 200‐300 milliseconds [34]. Other subcortical regions elicited pupil dilation with larger delays, which indicated an indirect activation of the LC [35]. In an optogenetic mouse model, pupil dilation marked relative changes in LC-NE activity, whereas variability challenges pupil size as a readout of absolute LC-NE activity [36]. This can be addressed by the application of baseline-corrected metrics [37]. In humans, the assessment of LC-NE activity is difficult with magnetic resonance imaging and electroencephalography (EEG) due to the LC’s location and small size [38]. This is pronounced in children that often induce more movement artifacts. Pupillometry now provides an index of LC-NE tonic and phasic activity (BPS and SEPR) that can be reliably measured with eye tracking. This innovative neuroimaging allows us to assess LC-NE functioning even in preschoolers in a clinical setting [5].

### LC-NE Functioning in an Etiological Model of Dispositional Risks and Stress

Psychopathology often develops by an interaction of dispositional risks and stress [39]. Dispositional risks describe internal features that increase a latent burden. In children, stress often refers to adverse childhood experiences like neglect and further extends to psychosocial domains like peer victimization [40]. If sufficient stress occurs upon dispositional risks, a psychopathology may develop. The preschool age is sensitive to this interaction and describes a precursor phase of lifetime psychopathology [15]. In preschoolers, dispositional risk profiles are observed, which map to polygenic scores for MHD that develop much later [11]. We propose that the LC-NE functioning in preschoolers underlies dispositional risks and shapes risk trajectories across diagnoses.

#### Dispositional Risks for Psychopathology and the LC-NE

Temperament describes a child’s innate sensory processing of affective stimuli and can represent an early dispositional risk [41]. Negative emotionality is a temperament with a proneness to negative affect that relates to later psychopathology and neuroticism. Negative emotionality has been associated with an elevated neurophysiological reactivity to reward and punishment, which explained an association between MHD polygenic scores and the p-factor in children [42]. This elevated reactivity has been reflected in an increased activity of the amygdala and the salience network and decreased activity of the ACC [43]. The LC-NE connectivity with the amygdala and ACC [44] suggests an effect of LC-NE functioning on negative emotionality.

#### Irritability

Irritability is a temperament trait of negative emotionality that is described by anger after frustration and attenuated fear under threat [45]. Irritability in children is the most pressing problem reported by help-seeking families [46]. Increased irritability predicted later conduct problems [47] and has been associated with a genetic risk for attention deficit hyperactivity disorder [48]. In contrast, irritability also predicted later internalizing [49]. This multifinality has been differentiated by error-related negativity (ERN) in EEG. In preschoolers with high irritability, increased ERN predicted later internalizing, while decreased ERN predicted later externalizing [50]. The ERN indicates an automated error detection that is modulated by LC-NE phasic activity [51]. Attenuated LC-NE phasic activity further attenuates a limbic fear response, which might promote externalizing behavior in irritable children [52]. We propose LC-NE phasic activity as an irritability correlate that differentiates between later externalizing and internalizing.

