**Figure 3. F3:**
[figure not shown]
Work program of LOCUS-MENTAL with time flow, required personnel, and the associated tasks.

#### Objective 1

This study aims to validate a concise test battery assessing LC-NE system functioning in preschool children using pupillometric measures during passive tasks. The test battery will be evaluated for convergent and discriminant validity.

#### Objective 2

This study aims to associate LC-NE functioning with correlates of psychopathology in a cross-sectional study. Task 2.1 will determine whether LC-NE functioning profiles serve as markers of dispositional risks and differentiate between irritability and behavioral inhibition. Task 2.2 will examine whether LC-NE functioning further mediates the association between childhood adversity and transdiagnostic psychopathology.

#### Objective 3

This study aims to evaluate the prospective effect of LC-NE functioning in a developmental model of vulnerability and stress. Task 3.1 will investigate whether pupillometric measures of LC-NE functioning in preschool age predict risk for psychopathology at school age. Task 3.2 will assess LC-NE functioning as a mediator between early stress responses and later psychopathology.

#### Objective 4

This study aims to develop an objective tool of risk prediction in the preschool ages based on the pupillometric measures of LC-NE functioning. LC-NE function profiles in preschoolers define a normative development space, where individual deviations indicate quantitative risks for MHD.

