##### Experimental Design

Cross-sectional analysis of combined pupillometry, EEG, and behavioral and cognitive assessments.

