##### Statistical Analysis Plan

We will apply LMM analysis with participants as random intercepts. These will allow us to explore associations between variables on a per-task level and control for potential covariates (age, gender, and IQ).

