##### Expected Outcome and Study Hypotheses

Behavioral inhibition (BIQ score) is expected to correlate positively with both BPS and SEPR in the pupillometric battery of LC-NE functioning. In contrast, irritability (assessed via ARI score) is expected to show differential profiles of LC-NE functioning. We expect high irritability scores and high SEPR to be associated with higher internalizing symptoms, while high irritability scores and low SEPR will be associated with higher externalizing symptoms—these expected outcomes are supposed to match ERN profiles [101]. Furthermore, in the neurocognitive paradigms, participants with high-irritability-low-SEPR profiles are further expected to show increased attentional bias toward threat cues (threat perception) and decreased attentional shifts during frustration (frustrative reward learning). These patterns would suggest a subgroup with elevated risk for conduct disorders. We will further explore LC-NE functioning in children with both high irritability and high behavioral inhibition, who are expected to exhibit higher negative emotionality and an increased BPS as an index of an elevated LC-NE tonic activity.

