##### Behavioral Measures

At each timepoint assessment of the behavioral measures, as described in Task 2.2, will include caregiver questionnaires (CBCL 4‐18) and the multiple-source assessment of childhood adversity (see Table 1).

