##### Expected Outcome and Study Hypotheses

This core of LOCUS-MENTAL will be informed by the outcome of task 2.2. We expect (see Figure 1) that higher BPS as an index of LC-NE tonic activity predicts a higher p-factor. Increased and decreased SEPR as an index of LC-NE phasic activity is expected to predict higher internalizing and externalizing symptoms, respectively. This would predict future psychopathology based on pupillometric markers. The stability of the investigated constructs is controlled for by autoregressive effects. The structural equation models will be explored for the covariate effects of childhood adversity, previous psychopathology, and received clinical support (eg, in the context of the outpatient clinic for early detection).

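### The irritability-specific claim about later internalizing versus externalizing is planned only as a cross-sectional analysis (Task 2.1); Task 3.1 tests the pupillary response prospectively but without irritability

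*Protocol article*

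**What the plan says.** **Hypothesis.** The Irritability section of the Introduction cites prospective evidence: in highly irritable preschoolers, the error-related negativity predicted which kind of psychopathology came later. It then proposes the analogous role for phasic activity: "We propose LC-NE phasic activity as an irritability correlate that differentiates between later externalizing and internalizing".

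**Task 2.1.** Objective 2 is introduced with "This study aims to associate LC-NE functioning with correlates of psychopathology in a cross-sectional study", and the Task 2.1 design is "Cross-sectional analysis of combined pupillometry, EEG, and behavioral and cognitive assessments". The analysis reads "We will apply LMM analysis with participants as random intercepts", with age, gender and IQ as potential covariates and no follow-up outcome. The expectation is "We expect high irritability scores and high SEPR to be associated with higher internalizing symptoms", with low SEPR and high irritability going with externalizing symptoms. After adding expected threat-bias and frustration-task patterns for the high-irritability, low-SEPR children, the section concludes: "These patterns would suggest a subgroup with elevated risk for conduct disorders".

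**Task 3.1.** An autoregressive cross-lagged panel model relates earlier baseline pupil size and SEPR to later CBCL factors. High SEPR is expected to predict internalizing and low SEPR externalizing, across all children. On covariates: "The structural equation models will be explored for the covariate effects of childhood adversity, previous psychopathology, and received clinical support". Irritability is not named as predictor, moderator or covariate.

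**Data.** Table 1 lists the irritability scale (ARI) and the CBCL for objectives 2.1 to 3.2. For Task 3.1: "At each timepoint assessment of the behavioral measures, as described in Task 2.2, will include caregiver questionnaires", and these include the CBCL.

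**The concern.** The hypothesis has two features: it concerns irritable children, and it concerns later symptoms. Each planned analysis captures one of them. Task 2.1 has irritability but no follow-up; Task 3.1 has follow-up but no irritability. No stated analysis joins the two.

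This matters because a concurrent irritability-by-SEPR pattern may reflect a marker of future divergence, a correlate of symptoms already present, or an effect of those symptoms on the pupil. Nor can the Task 3.1 main effect stand in for the missing term. If SEPR matters mainly in irritable children, an average over all children dilutes the effect; if its direction reverses with irritability, the average can be zero. Work Package 4 draws on the findings of Objectives 2 and 3 for the individual risk model, so a concurrent result read as risk could carry forward into the tool.

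**Working it through.** **The plan's own figure.** Task 2.1 states power 0.84 for n=140 and b=0.3. A Fisher-z calculation for r=0.3 (two-sided alpha 0.05, assumed) gives 0.952 at n=140 and 0.855 at n=98. The stated figure comes from a mixed-model simulation whose variance components are not given, so a closed form neither confirms nor refutes it. It is not disputed here: it concerns an association of LC-NE functioning with dispositional risk, not the irritability-by-SEPR term.

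**Inputs from the protocol.** Task 2.1 n=140 with about 30% attrition: 140 × 0.70 = 98. Cohort 300 with the cited meta-analytic mean retention of 73.5%: 300 × 0.735 ≈ 220.

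**Assumed inputs.** Standardized scores; ARI effect on the CBCL of 0.4; one-year CBCL stability of 0.6; two-sided alpha 0.05. No document gives an interaction size. With y1 the baseline and y2 the later CBCL score:
- y1 = 0.4·ARI + g·(ARI × SEPR) + error
- y2 = 0.6·y1 + h·(ARI × SEPR) + error

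**Step 1: concurrent but not prospective, large-sample coefficients.** Here the ARI main effect was left out, the interaction on y1 was set to 0.30 with h = 0, and stability was varied from 0.5 to 0.8.
- On y1: 0.30.
- On y2, unadjusted: 0.30 × 0.5 = 0.15 up to 0.30 × 0.8 = 0.24.
- On y2, adjusted for y1: 0.00.

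Even an unadjusted follow-up analysis would show an association that is only carried-forward baseline symptoms, so the baseline adjustment is essential.

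**Step 2: how often each test is significant.**

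| Assumed truth | Cross-sectional test | Prospective test, adjusted for y1, n=220 |
|---|---|---|
| g = 0.2, h = 0 | about 55% (n=98) to 71% (n=140) | about 5% |
| g = 0, h = 0.15 | about 5% | about 76% |

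The 5% entries follow by construction, because the relevant effect was set to zero. They illustrate that the two tests answer different questions and are not evidence about this study. The other entries move with the assumed size: cross-sectional power runs from 19% (g = 0.1, n=98) to 97% (g = 0.3, n=140).

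**Step 3: what the prospective model could detect.** At n=220 and stability 0.6, simulated power is about 76% at h = 0.15, 44% at 0.10 and 14% at 0.05. A hand check agrees approximately: residual SD ≈ √(1 − 0.6²) = 0.8, so the standard error is ≈ 0.8/√220 = 0.054. Power is then Φ(0.15/0.054 − 1.96) ≈ 0.79, Φ(0.10/0.054 − 1.96) ≈ 0.46 and Φ(0.05/0.054 − 1.96) ≈ 0.15. Varying stability from 0.5 to 0.8 moves the 0.15 case from about 72% to 95%. The 95% confidence interval would be roughly ±1.96 × 0.054 = ±0.11.

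**The case against.** A reader might infer that the whole hypothesis about later symptoms is tested only on concurrent CBCL, that concurrent symptoms are passed off as risk, and that the follow-up data go unused. The documents do not support that reading.

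- Task 3.1 tests the SEPR main effect on later internalizing and externalizing with autoregressive control, which is also the expectation in the Behavioral Inhibition section. Only the irritability-specific term lacks a prospective test.
- Objective 2 is openly labelled cross-sectional, and the Task 2.1 expectation speaks of association without the word later. The risk sentence is conditional and also rests on the neurocognitive patterns, not on the CBCL alone. Irritability is itself presented, with cited prospective evidence, as a dispositional risk.
- Table 1 assigns ARI to the longitudinal objectives, and the Task 3.1 covariates are listed for exploration, not as a closed set. A separate analysis plan could name further moderators.
- The Task 2.1 text does not say that its 140 children are assessed at T1 or belong to the 300. The Figure 4 legend supports nesting only in general terms.

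These points narrow the concern, and the analysis-plan point has weight: an unnamed moderator alone would be no finding. What remains is on the page. The article states a conditional claim about later outcomes, fixes the one analysis that combines irritability with SEPR as cross-sectional, and draws a risk reading from it. The limited power of the proposed model is also a fair objection; it governs how a null result is reported and does not make the concurrent test a substitute.

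**Conclusion.** The concern holds in its narrow form: the irritability-specific differentiation of later outcomes has no stated prospective test, and a concurrent pattern is read as suggesting elevated risk. It is a mismatch between one hypothesis and its planned analysis. It does not touch the primary aim or the core Task 3.1 model, and the remedy is an inexpensive improvement.

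The qualitative conclusion, that a concurrent interaction can be present without prospective differentiation and absent when differentiation exists, does not depend on the assumed numbers. The percentages do. They rest on assumed interaction sizes, an assumed ARI effect and CBCL stability, a baseline CBCL measured without error, two-sided alpha 0.05, and n=220 from a meta-analytic retention figure that is not a projection for this study.

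**What to change.** 1. Add to Task 3.1 one pre-stated secondary model in the full cohort: CBCL internalizing and externalizing at T2/T3 on T1 ARI, T1 SEPR and ARI × SEPR, adjusted for T1 CBCL, age and gender. State the expected signs: positive product term for internalizing, negative for externalizing.
2. Describe the Task 2.1 irritability-by-SEPR result as a concurrent association, and let any statement about later risk rest on the prospective model.
3. Confirm that ARI is collected at T1 in all 300 children. Table 1 implies this by listing it for 2.1 to 3.2, but the Behavioral Measures text of Tasks 2.2 and 3.1 does not name it.

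Cost: no new visit or instrument if Table 1 is followed, and one more secondary analysis over two outcomes. Task 2.1 can claim less on its own. Because power is limited for small interactions, a null result should be reported with its confidence interval and not as a decisive refutation. The longitudinal study is scheduled to start in April 2026, so the model can be fixed before any follow-up data exist.
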